### Sample size {14}

A total sample size of 136 participants will be required (68 participants per trial arm, prior to accounting for drop-out), based on the primary outcome of an improvement in radiological healing by two Fredericson grades or more, or reduction to grade zero, 8 weeks after randomisation. The sample size was determined using data from Almirol and colleagues’ (2016) 8 week randomised controlled trial in adults aged 21–45 years with recent lower-extremity stress fractures (35). Almirol et al. (2016) reported 67% of participants who received teriparatide achieved a two grades or more improvement in healing or reduction to grade zero (i.e. ‘success’); compared with 43% of participants in the placebo group [35]. Assuming a 20% drop-out rate during the first 8 weeks of the present study, 108 participants (54 participants per trial arm) will complete an MRI scan at week 8; thereby providing 80% statistical power to detect a between group difference (two-sided test, significance level of 5%), if the ‘success’ rate is ≥ 71% in the intervention arm (chi-squared test with continuity adjustment). This equates to an odds ratio of 3.23 or a relative increase in healing of approximately 65%.

### Recruitment {15}

Potential participants with single or multiple lower body stress fractures diagnosed by MRI will be identified by physiotherapists and general practitioners at Infantry Training Centre, Catterick. Potential participants will be given a participant information sheet and will be invited to meet investigators for a detailed explanation of the study as soon as practicable. The planned recruitment period (18 months) has been calculated using the most recent data on rates of lower body stress fracture injuries during Infantry training to enable the study to reach the target sample size.

## Assignment of interventions: Allocation

### Sequence generation {16a}

Eligible participants who provide written, informed consent will be randomised on a 1:1 basis to one of two trial arms using a web-based randomisation process (REDCap). Allocation will be made after eligibility has been confirmed. This process will use blocked randomisation with block lengths of 2–6 in random order. Allocation will be stratified by vitamin D status, measured at baseline (serum 25-hydroxyvitamin D < 30 nmol/L, deficient; or ≥ 30 nmol/L, not deficient), and whether the participant has single or multiple lower body stress fracture sites.

### Concealment mechanism {16b}

Randomisation will be performed centrally using a web-based randomisation process (REDCap).

### Implementation {16c}

The randomisation schedule will be generated by Norwich Clinical Trials Unit (NCTU). Eligible participants will be enrolled by an appropriately trained clinician or delegated member of staff at the NHS institution who will randomise participants using the web-based study database.

## Assignment of interventions: Blinding

### Who will be blinded {17a}

All MRI scans (primary outcome) will be assessed by two musculoskeletal consultant radiologists; all blood and urine biochemical analyses will be completed by technicians; and bone density and morphology images will be reviewed at the end of the study by an independent assessor, all of whom will be blind to the randomisation outcome.

### Procedure for unblinding if needed {17b}

This is an open label design and neither participants nor investigators will be blind to the randomisation outcome. There will be no expected circumstances where the radiologists, technicians or bone density and morphology image assessor will need to be aware of a participant’s allocated intervention.

## Data collection and management

### Plans for assessment and collection of outcomes {18a}

Investigators will be trained centrally in the use of data collection instruments, laboratory equipment, questionnaires, case report forms, and data entry onto a central database. Investigators will follow standard operating procedures and working instructions to help ensure valid and reliable data are collected. Standardising these processes will enhance data quality and reduce bias by detecting and reducing the quantity of missing or incomplete data, inaccuracies, and excessive variability in measurements [47]. Screening and eligibility data will be collected by investigators using case report forms prior to allocation (Fig. 2). Radiological healing will be assessed by two musculoskeletal consultant radiologists blind to the randomisation outcome, using Fredericson grading of MRI [39, 40], and will be recorded using case report forms. Clinical healing will be assessed by investigators using a standardised protocol and case report form [41]. The date of the initial decision to discharge from Army physical rehabilitation will be obtained from participants’ Army medical records and recorded by investigators using case report forms. The SF-36 questionnaire will be completed by participants to assess health-related quality of life [44, 45], and investigators will verbally ask participants the questions in the C-SSRS questionnaire to assess depression. Participants will record their pain on a visual analogue scale [42, 43]. Investigators will ask participants to report adverse events and their use of concomitant medications, which will be recorded using case report forms. Participants’ alcohol consumption and smoking habits will be recorded by investigators completing case report forms. In accordance with standard operating procedures, physical activity levels will be assessed using accelerometers (in a minimum of 10 participants in each of the control and intervention arms), venous blood samples will be collected by investigators, urine samples will be collected by participants, and blood and urine biochemistry will be analysed by technicians blind to the randomisation outcome (Table 1). Pregnancy tests will be conducted according to standard operating procedures. Bone density and morphology will be assessed by investigators using DXA, pQCT and HR-pQCT, according to standard operating procedures, with a random sample of analysed images (≥ 10%) reviewed at the end of the study by an independent assessor blind to the randomisation outcome. Physical fitness will be recorded by investigators accessing participants’ Army fitness records. Army medical records will be reviewed by investigators to record any subsequent bone injuries and fractures.

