### Objectives {7}

The primary objective of the RETURN trial is to investigate the effect of teriparatide in addition to usual Army standard care on lower body stress fracture healing in military recruits, compared with usual Army standard care alone. The primary outcome will be the improvement in radiological healing, assessed using Fredericson grading of MRI, by two grades or more, or reduction to grade zero, 8 weeks after randomisation. Secondary objectives are to examine the effect of teriparatide on (i) time to radiological healing; (ii) time to clinical healing, assessed by clinical severity score calculated from injury signs and symptoms; (iii) time to discharge from Army physical rehabilitation; (iv) pain symptoms; (v) health-related quality of life; and (vi) adverse events. It is hypothesised that treatment with teriparatide will accelerate (i) the rate of radiological healing of lower body stress fractures; (ii) the cessation of pain associated with the injury; and reduce (iii) the time taken to return to Army training, compared with standard care alone. The effect of teriparatide on the following exploratory outcomes will also be investigated: (i) blood and urine biochemistry; (ii) bone density and morphology; (iii) physical activity levels; and (iv) long-term future fracture rate.

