##### Long-term future fracture rate

Participants’ Army medical records will be reviewed for 5 years after their final study visit to record any subsequent bone injuries and fractures.

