### Perspectives and future directions

If the study finds teriparatide to be effective for accelerating stress fracture healing, military recruits injured with lower body stress fractures could be treated with teriparatide as part of their standard care, subject to balance of investment and health economics analysis, approval by the Army Drugs and Therapeutics Committee, and incorporation into the Army stress fracture treatment protocol. The long-term future fracture rate recorded in the study will provide an insight into the fracture preventative potential of teriparatide in young, otherwise healthy adults. Investigating the efficacy of teriparatide administered using an alternative delivery route that would eliminate the need for daily subcutaneous injections would be of interest. Oral dosing is potentially a more convenient method of administering teriparatide [56]; however, it is currently being investigated in early phase clinical trials and was not available for the present study.

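### The exploratory 5-year review of Army medical records is done by investigators who know the allocation, so ambiguous bone-injury entries could be classified differently by arm

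*Protocol article*

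**What the plan says.** The outcome is the last of four in the list that Objectives {7} introduces with "The effect of teriparatide on the following exploratory outcomes will also be investigated", and it is named there as the long-term future fracture rate. Under its own heading among the exploratory outcomes, the protocol says that participants' Army "medical records will be reviewed for 5 years after their final study visit to record any subsequent bone injuries and fractures". Plans for assessment and collection of outcomes {18a} assigns the work: "Army medical records will be reviewed by investigators to record any subsequent bone injuries and fractures".

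Procedure for unblinding if needed {17b} says: "This is an open label design and neither participants nor investigators will be blind to the randomisation outcome". Who will be blinded {17a} lists the radiologists reading the MRI scans, the technicians running the biochemistry, and one further group: "bone density and morphology images will be reviewed at the end of the study by an independent assessor, all of whom will be blind". The record review is not on that list.

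Perspectives and future directions gives the intended use: the long-term fracture rate "will provide an insight into the fracture preventative potential of teriparatide in young, otherwise healthy adults".

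**The concern.** Taken together, these sections fix both who extracts the 5-year outcome and that those people know the arm. What they collect, "to record any subsequent bone injuries and fractures", is wider than the outcome's name. A fracture with an imaging report leaves the extractor little to decide. An entry short of that may call for a judgement on whether it belongs, and a person who knows the allocation could make that judgement differently in the two arms without intending to.

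The choice also sits oddly with the rest of the plan. The biochemistry and the bone density and morphology measures are exploratory too, yet the laboratory work is masked throughout and at least 10% of the analysed bone images are checked by a masked assessor. The Protocol amendments section defends the open-label design by the objectivity of the MRI endpoint, and that argument does not extend to unmasked classification of routine records.

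At stake is the credibility of an exploratory estimate on a question for which, by the Background, there are no studies in young adults. Events may be few, in which case each borderline entry carries weight.

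**Working it through.** **The text.** Extraction is by investigators ({18a}). Investigators are not blind ({17b}). The masked list covers MRI reading, biochemistry and bone-image review ({17a}). The exposure therefore follows from what is stated and not from silence.

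**Would hiding the allocation field mask these reviewers?** Not reliably. Investigators train participants to inject, review injection diaries every 4 weeks (Intervention description {11a}; Strategies to improve adherence {11c}), and meet participants at least every 4 weeks and as often as daily on site (Plans to promote participant retention {18b}). They are likely to remember who was treated.

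**Size.** The protocol states no event rate, effect size or power for this outcome, so there is no figure to reproduce. The only input from the document is 68 per arm (Sample size {14}). Everything else below is assumed, with complete follow-up and no true effect.

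*Illustration 1: a few entries moved.* Expected events per arm are e = 68 × assumed rate. If m entries are left out in the teriparatide arm and m added in the control arm, the risk ratio is (e − m)/(e + m).

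| Assumed rate | e | m = 1 | m = 2 |
|---|---|---|---|
| 10% | 6.8 | 5.8/7.8 = 0.74 | 4.8/8.8 = 0.55 |
| 20% | 13.6 | 12.6/14.6 = 0.86 | 11.6/15.6 = 0.74 |
| 30% | 20.4 | 19.4/21.4 = 0.91 | 18.4/22.4 = 0.82 |

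All the errors here favour teriparatide, which is the least favourable pattern for a given m.

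*Illustration 2: only ambiguous entries exposed.* Let a proportion p of each arm have a clear fracture and a proportion q an ambiguous bone injury. Ambiguous entries are counted with probability a in control and b in teriparatide. The observed risks are p + qa and p + qb.

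| p | q | Risk ratio, a = 60%, b = 40% | Risk ratio, a = 80%, b = 40% |
|---|---|---|---|
| 5% | 5% | 0.07/0.08 = 0.88 | 0.07/0.09 = 0.78 |
| 5% | 10% | 0.09/0.11 = 0.82 | 0.09/0.13 = 0.69 |
| 10% | 5% | 0.12/0.13 = 0.92 | 0.12/0.14 = 0.86 |
| 10% | 10% | 0.14/0.16 = 0.88 | 0.14/0.18 = 0.78 |

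By the normal approximation at 68 per arm, a two-sided 5% test would then reject with probability 5.4% to 6.7% in the 60/40 case and 6.4% to 11.5% in the 80/40 case.

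**Against chance.** For a risk ratio of 1.00 the standard error of its logarithm is √[2(1/e − 1/68)], which is 0.51, 0.34 and 0.26 for the three rates. The approximate 95% intervals are 0.37 to 2.74, 0.51 to 1.96 and 0.60 to 1.67. Every shift in illustration 1 lies inside the matching interval.

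**The case against.** The strongest reply is that little rests on this outcome and that masking at the desk leaves the larger problem untouched.

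- **Bias upstream.** Participants know their arm, so care-seeking, imaging and the wording of the records may already differ before anyone extracts anything. This stands. A reader might infer that masking would remove the bias at almost no cost. The documents do not support that: they give no costs, the records may name the treatment and need redaction, and a list without allocation would not mask people who have dealt with the participants for months.
- **Weight of the outcome.** It is exploratory, and only an insight is promised. Any change to standard care is tied to stress fracture healing. Power is also low: with 68 per arm, a true halving would be detected with probability about 12%, 20% or 37% at assumed control rates of 5%, 10% or 20%. This stands and keeps the point minor. It does not answer the concern, since sparse events make each borderline entry count for more.
- **What is counted.** The protocol names bone injuries and fractures separately and does not say that the former enter the fracture rate. Diagnoses come from treating clinicians, so investigators' judgement mainly concerns unclear entries. This stands too, and is why clear fractures are set aside here.
- **Missing detail.** Definitions and coding rules may sit in the full protocol, the SAP or the working instructions that {18a} mentions. Their absence from an article is no finding. But {18a} and {17b} fix the unmasked reviewer in the article itself.

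**Conclusion.** The point holds as a minor one. The article assigns classification of the 5-year record entries to people who know the arm, and the entries include a category wider than fracture. Ambiguous entries are exposed to differential classification, while clear fractures are little exposed.

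No size can be established. The shifts to between 0.55 and 0.91 in the first illustration and between 0.69 and 0.92 in the second rest on assumed rates, complete follow-up and errors that all run one way. They show that modest differential handling could matter to the estimate, not that it will occur. A reader might take them to mean that a false preventive effect is likely to be declared. The figures do not support that: the shifts in the first illustration are within chance variation, and moderate differential counting (60% against 40%) raises the false-positive rate only to about 5.4% to 6.7%. Nor does the point touch the primary outcome, its sample size or its power.

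**What to change.** Amend {18a} in four respects:

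1. Extract all bone-related entries for every participant in both arms.
2. Classify them by fixed rules, based on the recorded diagnosis and the imaging report, set before the review begins.
3. Have any entry the rules do not settle classified from extracts that carry the PIN only, with mentions of treatment removed, by existing trial personnel who had no contact with the participants. Add this step to the list in {17a}.
4. Report fractures, which match the outcome's name, separately from other bone injuries.

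The cost is the time to write the rules, code the entries and redact the extracts. Sample size, follow-up and the primary analysis do not change. The report should say that the step reduces bias at extraction and classification, and that differences arising from participants' knowledge of their arm remain.

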
### Plans to promote participant retention and complete follow-up {18b}

Investigators will maintain regular contact with participants throughout their participation in the trial to offer support as required. Participants will be asked for their preference with regards to the form this will take (i.e. telephone or video calls, text messages, emails, face-to-face consultations). All participants will meet with investigators a minimum of every 4 weeks. Participants who remain onsite at Infantry Training Centre, Catterick will meet with investigators as frequently as every day. Study visits will be scheduled to avoid disruption to each participant’s rehabilitation programme, with the aim to incorporate the trial into routine life within their barracks. Participants who discontinue or deviate from their allocated intervention protocol will remain in the trial for all follow-up visits, provided they are willing. For participants who withdraw or are withdrawn from the study, all data collected up to the date of withdrawal will be retained for use in the study. The reason for withdrawal, if given, and loss to follow-up will be recorded.

### Data management {19}

Each participant will be given a unique trial participant identification number (PIN). Data will be recorded on paper case report forms first and will then be entered under the participant’s PIN onto a central database (REDCap) stored on secure servers at the University of East Anglia. Data will be recorded and entered by investigators (trained for data entry) at Infantry Training Centre, Catterick and the NHS institution. The database will be accessed using unique, individually assigned usernames and passwords, with access limited to study investigators, the Trial Team at NCTU, and external regulators if required. The type of activity a user may undertake will be controlled by the privileges associated with their personal password-protected account and REDCap data access groups. A full audit trail of data changes will be maintained prior to the data lock. Data integrity will be ensured by using referential data rules, and valid value, range, and consistency checks. Staff at NCTU will review case report form data for errors and missing key data points. The trial database will also be programmed to generate reports on errors and error rates.

Servers at the University of East Anglia are protected by firewalls and are patched and maintained according to best practice. The location of the servers is protected physically and environmentally in accordance with the University of East Anglia’s General Information Security Policy 3 (Physical and environmental security). The database and associated code have been developed by NCTU Data Management, in conjunction with the Trial Team. The database software provides several features to help maintain data quality, including maintaining an audit trail, allowing custom validations on all data, allowing users to raise data query requests, and search facilities to identify validation failure/missing data. After completion of the trial, the database will be retained on University of East Anglia servers for on-going analysis of secondary and exploratory outcomes.

### Confidentiality {27}

Paper copies of personal data will be kept at trial sites in a secure location with restricted access. Following consent, identifiable data will be kept on the trial database to allow investigators to contact participants in order to arrange study visits. Only authorised Trial Team members will have password access to this part of the database, and this information will be destroyed one month after closure of the study. The confidentiality of participants’ personal data will be ensured by not recording participant names on case report forms and limiting access to personal information held on the NCTU database. The PIN will be the primary identifier for a participant, with secondary identifiers of their date of birth and initials. The participant’s consent form will carry their name and signature and will not be kept with any additional participant data. The identification, screening and enrolment logs, linking participant identifiable data to the pseudoanonymised PIN, will be held locally and securely by trial sites. Trial records will be archived by Norfolk and Norwich University Hospitals NHS Foundation Trust (NNUH) as per current regulatory requirements. Data will be handled in accordance with provisions of the General Data Protection Regulation (EU) 2016/679 and the Data Protection Act 2018.

### Plans for collection, laboratory evaluation and storage of biological specimens for genetic or molecular analysis in this trial/future use {33}

No specimens will be collected for genetic or molecular analysis.

## Statistical methods

### Statistical methods for primary and secondary outcomes {20a}

A full statistical analysis plan (SAP) will be developed by the Trial Statistician and Chief Investigator before the final data lock and will be submitted to the independent Data Monitoring Committee (DMC) and Trial Steering Committee (TSC) for approval [48]. The primary efficacy analysis will be based on the intention-to-treat principle in which all participants will be analysed according to the trial arm to which they were allocated, regardless of compliance. The primary outcome (radiological healing by two Fredericson grades or more, or reduction in grade to zero, 8 weeks after randomisation) will be analysed using a logistic regression model. This model will include the baseline stratification variables (vitamin D status and single or multiple lower body stress fractures); anatomical site of fracture; baseline MRI grade; allocated trial arm; and any other baseline prognostic variables pre-specified in the SAP. The estimate of efficacy will be the between group difference from the analytical model, calculated with 95% confidence intervals and with statistical significance set at the 5% level (two-sided). Secondary outcomes will be analysed in an analogous manner, i.e. using appropriate statistical models with stratification variables, additional specific prognostic variables (including the baseline value of the outcome where available) and allocated trial arm. A secondary analysis of MRI grading at each time point using a logistic regression model with a generalised estimating equation approach to parameter estimation and a specified auto-regressive correlation structure, i.e. to allow for the correlation in outcome between timepoints, will also be completed.

